#### Laboratory definition of dengue infection

##### *Evidence of recent dengue virus infection*

This is defined as detectable IgM dengue antibody, or positive dengue PCR and/or NS1 Antigen, as sampled from the passive and active surveillance.

##### *Dengue virus infection during the study period*

This is defined by quantitative dengue IgG ELISA, as a fourfold increase in antibody titres against any dengue virus serotype between the baseline and end of study specimens in paired sera.

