### Design

A cluster-randomised, double-blinded, crossover design will be implemented. Randomisation will be by school. An individual participation rate of at least 90% within each school is anticipated. The schools will be randomised into two equal groups, with each school receiving impregnated uniforms in either the first (2012–13) or second (2013–14) annual transmission season covered by the trial.

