### Sample size

Sample size for the trial will take into account likely levels of dengue incidence, as well as the considerable wide-area variation in transmission from season to season, and local area (i.e., per school) variation [31]. Such large potential variations are unpredictable and difficult to quantify. The advantage of the crossover school-randomised design – which can be interpreted as a cluster-randomised design in relation to individuals – is that if there are particular factors driving local area variation from year to year (such as mosquito breeding sites close to schools), those sources of variation will, to some extent, be controlled by the crossover design. This design efficiency is a considerable advantage, notwithstanding the relatively large design effect that needs to be

applied to the overall sample size in recognition of the cluster randomisation and the considerable uncertainties around wide-area incidence rates from year to year.

In view of the probable large size of these variations and their inherent uncertainty, a design factor of 3 is used.

A design factor greater than unity is justified because of the school clustering effect. Unfortunately, because of the paucity of knowledge of dengue epidemiology, both in terms of year-on-year variation and its determinants in Thailand in general, and compounded by possible local variations in dengue that might occur between school locations, it is impossible to make detailed calculations of the required design effect. The choice of 3 as the design effect was therefore adopted as a conservative estimate in the absence of being able to make any better estimate.

The basic assumptions underlying the sample size for the trial are an incidence rate (symptomatic plus asymptomatic) of an average of 5% during a transmission season [32], i.e. 10% over two seasons; an aim of halving incidence by using impregnated uniforms (since any smaller effect would not be of policy interest) and a dropout rate (children leaving the school, etc.) of 20%.

According to Schouten and Kester [33], the overall sample size for a non-clustered crossover design can be calculated as

$$2n = \frac{[z_1 - \alpha/2\sqrt{\pi_A(1 - \pi_B) + \pi_B(1 - \pi_A)} + z_1 - \beta\sqrt{\pi_A(1 - \pi_A) + \pi_B(1 - \pi_B)}]^2}{(\pi_A - \pi_B)^2}$$

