#### Determining new dengue infections during the study period

Blood samples will be collected via venipuncture (2 ml) or finger prick (<0.2ml) from all study subjects at the beginning of the school term (June 2012) and at the end of the first study period (November 2012). Dengue IgG ELISA (with titres) will be measured at the Center of Excellence for Vectors and Vector-Borne Diseases (CVVD), Faculty of Science, Mahidol University at Salaya. The paired serum samples from each volunteer will be screened quantitatively for anti-dengue IgG antibodies by ELISA using a standardised protocol and reagents.

Passive and active surveillance for dengue and febrile episodes will be maintained throughout the study period (school term).

The parents of any child treated for a febrile episode during the study period will be asked to bring their child to the nearest health facility if the child does not show improvement within 48 h. When such study subjects report to a health facility, government nurses or doctors will treat the child following national guidelines and inform the study nurses or local public health officers stationed in the study area. Blood samples for dengue IgM and IgG and dengue PCR will be taken if there is a fever > 37.5°C. In case the health centre has no facilities for taking blood, the child will be advised to go to a centre with such facilities. The blood samples will be sent to a specified laboratory centre in Bangkok.

To enhance passive surveillance, we will also undertake active surveillance of febrile episodes. During the school term, field assistants will daily check from the school records for children who have been reported as absent for 2 days. The caretakers of those children will be contacted to find out about the reason for absenteeism. For those children who are reported to be absent because of a febrile illness, a blood sample will be taken within 4 weeks after onset of illness to check for dengue IgM. Furthermore, any laboratory data and clinical information will be collected directly from the health centre

in case the child has gone to such a health centre or hospital.

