### Analytical plan

The primary endpoint is a comparison of the incidence rates of laboratory-confirmed dengue infections per person-time exposed up to failure (i.e. dengue infection) or censoring (i.e. moving away) between the intervention and control groups.

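### The serological case definition (baseline to end of study) does not match the stated bleeds, and the second crossover season has no stated serum pair

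*Protocol*

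**What the plan says.** Protocol, Design: schools are randomised to two sequences, "with each school receiving impregnated uniforms in either the first (2012–13) or second (2013–14) annual transmission season covered by the trial".

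Protocol, Determining new dengue infections during the study period: all subjects are bled "at the beginning of the school term (June 2012) and at the end of the first study period (November 2012"). No routine bleed is stated for 2013–14. The same section says that surveillance "will be maintained throughout the study period (school term").

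Protocol, Laboratory definition of dengue infection, gives two definitions:
- From surveillance: "This is defined as detectable IgM dengue antibody, or positive dengue PCR and/or NS1 Antigen, as sampled from the passive and active surveillance".
- From paired IgG: infection is defined "as a fourfold increase in antibody titres against any dengue virus serotype between the baseline and end of study specimens in paired sera".

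Protocol, Analytical plan: the primary endpoint compares "incidence rates of laboratory-confirmed dengue infections per person-time exposed up to failure (i.e. dengue infection) or censoring (i.e. moving away"), between intervention and control.

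Protocol, Sample size: the assumption is "an incidence rate (symptomatic plus asymptomatic) of an average of 5% during a transmission season", so asymptomatic infections are part of what the trial is sized on.

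Protocol, Safety considerations: children who leave in year 1 are replaced in May–June 2013.

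**The concern.** A crossover analysed by treated and control person-time needs to know in which season each infection occurred. Surveillance cases carry a date. Infections without fever do not; they appear only as a titre rise between two sera, so the timing of those sera decides which allocation they count under.

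The definition and the schedule disagree on the closing serum. The definition uses the end of the study; the schedule's last stated serum is at the end of the first study period. Applied as written, the definition gives one result covering both allocations. The schedule as written gives a season-specific result for 2012 and none for 2013. Neither supplies what the Analytical plan needs for both seasons.

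This belongs in the protocol, since a serum that was not drawn cannot be recovered by analysis.

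**Working it through.** **The plan's own figure.** The inflation chain reproduces: 508 × 1.2 × 1.1 × 3 = 2,011.7, stated as 2,012, or 1,006 per arm. The starting value does not: the printed formula with 10% vs 5%, two-sided 0.05 and 90% power gives (1.960 × √0.14 + 1.282 × √0.1375)² / 0.05² = 584, not 508. That is a separate matter. What follows uses the stated 1,006 per arm.

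**Reading A: one serum pair from baseline to the end of the two-season trial.** Let p1 and p2 be the untreated risks in seasons 1 and 2, and RR the risk ratio under treatment.
- Treated first: 1 − (1 − RR·p1)(1 − p2) = RR·p1 + p2 − RR·p1·p2
- Control first: 1 − (1 − p1)(1 − RR·p2) = p1 + RR·p2 − RR·p1·p2
- Control first minus treated first = (p1 − p2)(1 − RR)

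With RR = 0.5 (the Sample size section aims to halve incidence):

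| p1, p2 | Treated first | Control first | Difference |
|---|---|---|---|
| 5%, 5% (Protocol average) | 7.4% | 7.4% | 0 |
| 10%, 10% (the 10% vs 5% of the sample size calculation, taken per season) | 14.5% | 14.5% | 0 |
| 8%, 2% (assumed, mean 5%) | 5.9% | 8.9% | +3.0 points |
| 2%, 8% (assumed, mean 5%) | 8.9% | 5.9% | −3.0 points |

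The same halving gives no difference, a positive one or a negative one, depending on which season was larger. Two sequence proportions cannot identify three unknowns (p1, p2, RR).

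**Reading B: only the stated June and November 2012 bleeds.** The serological comparison is then season 1 alone, 5 schools against 5, without within-school control. Inputs:
- 1,006 children per arm and design effect 3 (Sample size).
- Dropout of 20% or none. The Protocol gives dropout no time frame, so both are shown.
- 5% vs 2.5% (the per-season assumption, halved) or 10% vs 5% (the rates used in the calculation).

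Effective n per arm: 1,006 / 3 = 335.3; with dropout, 1,006 × 0.8 / 3 = 268.3.

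Power = Φ{[δ − 1.96·√(2·p̄(1 − p̄)/n)] / √([pC(1 − pC) + pT(1 − pT)]/n)}, where pC and pT are the control and treated risks, δ = pC − pT and p̄ is their mean.

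Example, 5% vs 2.5%, n = 268.3: (0.025 − 1.96 × 0.01640) / 0.01637 = −0.437, so power is 33%.

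| Rates | No dropout | 20% dropout |
|---|---|---|
| 10% vs 5% | 69% | 59% |
| 5% vs 2.5% | 40% | 33% |

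The stated power is 90%. These figures count no surveillance cases and carry over the Protocol's design effect of 3 to a parallel comparison, which is an assumption.

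**Which infections are affected.**

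| Infection | Assignable to a season from the stated text? |
|---|---|
| Season 1, found by the June/November 2012 pair | Yes |
| Either season, found by surveillance (IgM, PCR, NS1) | Yes, dated |
| Season 2, asymptomatic | No stated serum pair |
| Season 2, asymptomatic, replacement child | No stated baseline either |

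**The case against.** The strongest reply is that a within-season pair was plainly intended. The November 2012 bleed would have no use in a pair spanning both seasons. Naming a first study period implies a second. The surveillance sentence equates the study period with the school term, and the definition sits under a heading about infection during the study period. The Sample size section has infected children take no further part, which presupposes that season-1 status is known. Much of this stands, and a per-season pair is the likely intent. It does not settle the text. Entomological collections uses the entire study period for testing over the whole trial, so the term is not fixed, and likely intent does not put a 2013 bleed in the schedule.

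A reader might also infer three stronger things that the Protocol does not support:
- *That infections cannot be assigned to a season at all.* The 2012 pair lies within one allocation, and surveillance cases are dated in both seasons. The primary endpoint is laboratory-confirmed infection, not paired serology alone.
- *That the baseline-to-end pair carries no treatment information whatever the effect.* That holds only for equal seasons. The Sample size section expects considerable variation between seasons, and the contrast is then non-zero but confounded with it.
- *That the trial plans no season-2 serology, with 33% power as the result.* The 2013 bleeds are unstated, not ruled out, and replacements would join when a start-of-term bleed would naturally fall. The 33% is the low end of a range and applies only if season-2 sera are never drawn.

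**Conclusion.** The point holds as a conflict between the case definition and the bleed schedule. Following either literally leaves asymptomatic infections wrongly pooled across allocations or unobserved in season 2, although they are counted in the incidence on which the trial is sized.

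On the two-season pair, the sequence difference is (p1 − p2)(1 − RR): zero at the Protocol's average of 5% in each season, and otherwise of a sign and size that depend on the seasons. If only the 2012 sera exist, power for the serological comparison is about 33–69% instead of 90%, on the assumptions shown. If season-2 sera are drawn at the start and end of that season and infection is judged within season, neither loss arises.

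**What to change.** Reconcile the bleed schedule with the definition of infection during the study period:

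1. Define serological infection separately for each season, as a fourfold rise between that season's own start- and end-of-season sera, attributed to the uniform allocated in that season.
2. State the 2013 start- and end-of-season bleeds for all participants, and say that the 2013 start-of-season serum is the baseline for replacement children.
3. Prespecify how a rise between the end of season 1 and the start of season 2 is handled. Excluding it from both conditions is one option. Because the Design section labels the seasons as annual (2012–13, 2013–14), this is a choice to be made openly.

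The text change is a few sentences and leaves the sample-size inputs unchanged. The material cost is a start-of-season bleed in 2013 if it is not already planned; an end-of-season bleed is already presupposed by the crossover.

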#### Entomological collections

Mosquito abundance in ten study schools will be measured. One BG sentinel trap per school will be randomly placed indoors at the beginning of the school day (8.30 am) and the mosquitoes will be collected at the end of the school period (3.30 pm). In addition, mosquitoes in

each classroom will be collected by portable vacuum aspirators operated for 5 min per classroom. In order to determine species composition of mosquitoes around the school areas, ten ovitraps per school will be randomly placed indoors and outdoors around the school areas and will be left for 7 consecutive days before collection. Eggs collected from ovitraps will be reared to adults and the species will then be identified in the laboratory. These measurements will be taken at baseline and then every 4 weeks to compare entomological changes between the intervention and control schools.

To determine whether there is loss of efficacy against mosquitoes, throughout the entire study period five items of clothing from the ten schools will be examined monthly. This will be done using standardised WHOPES-recommended cone tests.

### Economic analysis

Using a cost-of-illness approach [34], we will examine the economic impact of dengue infection in school-aged children at the household level. While considering the direct costs and indirect costs on households resulting from an illness episode, our analysis will exclude psychosocial costs that are difficult to estimate. A patient questionnaire will be administered to mothers/caretakers of children who have had a febrile illness episode. The questionnaire will document demographic and socioeconomic information of households, characteristics of the child's illness episode (average duration of fever and illness and symptoms), health-seeking behaviour (type and setting of care received), household spending (direct medical costs and non-medical costs), work and school absenteeism (number of days lost for paid work and from school), informal care costs (hours of patient care provided by household members), and household income lost because of child's illness episode.

The economic evaluation will include the cost-effectiveness analysis of insecticide-treated uniforms for the prevention of dengue infection based on the intervention efficacy and cost data derived from the trial. The cost-effectiveness analysis will follow standard guidelines of economic analyses and will be conducted from the societal perspective [35]. The intervention costs will be identified, measured and valued alongside the trial. Healthcare resource use data will come from the cost-of-illness study described above. Unit costs for ambulatory and inpatient care will be derived from national published data. Effectiveness will be measured in terms of dengue cases and DALYs averted because of the intervention. To assess the impact of uncertainty in key input variables on the cost-effectiveness results, we will undertake probabilistic uncertainty analysis using Monte Carlo simulations.

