#### Economic analysis

- To estimate the costs of dengue infection in school-aged children
- To estimate the costs and cost-effectiveness of impregnated school uniforms for the prevention of dengue in school-aged children

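### Resource use is measured while the trial itself prompts care-seeking, and nothing listed separates study-prompted contacts, so cost per dengue episode and costs averted are probably overstated

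*Protocol*

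**What the plan says.** Two parts of the protocol bear on this point.

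**Case finding** (Determining new dengue infections during the study period). Parents of a child treated for a febrile episode "will be asked to bring their child to the nearest health facility if the child does not show improvement within 48 h". At the facility, "government nurses or doctors will treat the child following national guidelines". There is then a possible further trip: "In case the health centre has no facilities for taking blood, the child will be advised to go to a centre with such facilities". Separately, school records are checked for children absent for two days: "The caretakers of those children will be contacted to find out about the reason for absenteeism". Those with febrile illness have a blood sample taken.

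**Costing** (Economic analysis, under Methods/Design). "A patient questionnaire will be administered to mothers/caretakers of children who have had a febrile illness episode". The listed content includes "health-seeking behaviour (type and setting of care received), household spending (direct medical costs and non-medical costs", together with lost work and school days, informal care and lost income. For the cost-effectiveness analysis, "Healthcare resource use data will come from the cost-of-illness study described above". Prices for outpatient and inpatient care are to come from published national sources. The analysis takes the societal perspective, measures effect as cases and DALYs averted, and handles uncertainty by Monte Carlo simulation.

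The first economic objective is "To estimate the costs of dengue infection in school-aged children"; the second is the cost and cost-effectiveness of the uniforms.

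**The concern.** The episodes that supply the cost data are the same episodes in which the trial prompts attendance. The request after 48 h may bring in children whose families would otherwise have stayed at home. The onward trip has no stated purpose except to obtain blood. Neither the listed questionnaire topics nor the described analysis identifies a contact that happened only because of the study, so its travel, tests and lost time can enter the cost of dengue.

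Both economic objectives depend on that cost. If it is higher than under usual care, each case averted appears to save more than it would outside the trial, and the cost-effectiveness ratio moves in favour of the uniforms. The Discussion already anticipates a cost-effective intervention, so a shift in that direction matters to how the result will be used.

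**Working it through.** The protocol gives no cost per case, visit rate or amount of costs averted, so there is no figure of its own to reproduce. The check has three parts.

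**1. Do other features of the plan remove the effect?**

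- National unit costs fix the price of a visit. The number of visits, household spending and lost time still come from the trial.
- Guideline treatment governs care after arrival. It does not govern whether the child arrives or travels on for blood.
- Monte Carlo simulation, as described, spreads uncertainty around the inputs. It does not correct inputs that are all shifted in one direction.
- Surveillance is the same in both blinded arms. That protects the efficacy comparison but not the level of cost per case.

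The last point can be shown with the usual form of the ratio, which the protocol does not spell out. Let I be the added intervention cost, A the cases averted and c the usual-care cost per case. Then

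ratio = (I − A·c)/A = I/A − c.

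If the measured cost is f·c, the ratio per case averted falls by (f − 1)·c, even when A is estimated without bias.

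**2. How large might f be?** All inputs are assumptions, because the documents give none:

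- p, the share of episodes with a facility visit in routine care: 50–90%
- q, the share in the trial: 70–100%, using only pairs with q ≥ p
- s, the share of routine episode cost that scales with visits: 25–75%

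Formula: f = 1 − s + s·(q/p).

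Example: p = 0.70, q = 1.00, s = 0.50 gives 0.50 + 0.50 × 1.429 = 1.21.

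| p | q | s = 25% | s = 50% | s = 75% |
|---|---|---|---|---|
| 50% | 70% | 1.10 | 1.20 | 1.30 |
| 50% | 90% | 1.20 | 1.40 | 1.60 |
| 50% | 100% | 1.25 | 1.50 | 1.75 |
| 70% | 70% | 1.00 | 1.00 | 1.00 |
| 70% | 90% | 1.07 | 1.14 | 1.21 |
| 70% | 100% | 1.11 | 1.21 | 1.32 |
| 90% | 90% | 1.00 | 1.00 | 1.00 |
| 90% | 100% | 1.03 | 1.06 | 1.08 |

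The range is 1.00 (no added visits) to 1.75. It counts at most one visit per episode, so onward trips for blood are not included.

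**3. Could earlier care offset this?** Let a be the outpatient share of episode cost, h the inpatient share, and r the fraction of inpatient cost avoided by earlier attendance. Then f = 1 + a·(q/p − 1) − h·r. With a = 0.30, p = 0.70 and q = 1.00, the first two terms give 1 + 0.30 × 0.429 = 1.129.

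- h = 0.40, r = 0.25: 1.129 − 0.100 = 1.03
- h = 0.40, r = 0.50: 1.129 − 0.200 = 0.93
- h = 0.60, r = 0.50 (the most extreme pair tried): 1.129 − 0.300 = 0.83

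So the sign can reverse, but only if earlier attendance avoids a large part of the inpatient cost.

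**The case against.** The strongest reply is that the protocol nowhere says study-driven costs will be counted. It ties the costs to the illness episode, says the analysis will follow standard guidelines, and only summarises the questionnaire. Item wording and exclusion rules may sit in the instrument or an analysis plan. This stands in part: it rules out calling the plan wrong on its face. But the reason for a contact has to be asked at the time. If it is not collected, no analysis plan can reliably recover it, and it is absent from a fairly detailed list of topics.

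Four stronger readings are tempting, and the documents do not support them.

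- *Costs come only from children sent to facilities.* The questionnaire covers febrile episodes generally. Absence checks will also find children who may have attended no facility, and their low costs pull the mean down. That does not take study-prompted trips out of the mean.
- *Study-prompted contacts cannot be separated.* The full instrument is not shown, and type and setting of care may identify some sampling-only visits. The supported statement is that no listed item does so.
- *Costs are certainly overstated.* The 48 h request is conditional, many such children might be taken anyway, and earlier care may lower inpatient cost. Such a saving would itself be produced by the trial, so the measured cost would still not be usual-care cost.
- *Extra trips add to the school days lost.* The children concerned are febrile and unimproved, or already absent for two days. Nothing shows that a clinic trip adds a day.

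**Conclusion.** The point holds in a limited form. The cost data come from episodes in which the trial prompts attendance, and no listed item or analysis step sets study-prompted contacts apart. The probable result is an overstated cost per dengue episode and overstated costs averted, to the advantage of the uniforms.

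The direction is likely but not fixed by the documents, and the size cannot be derived from them. The factor of 1.00 to 1.75 rests wholly on the assumed visit and cost shares; it includes no effect at its lower end and leaves out any offset from earlier care. It refers to whole-episode cost. A reader might take the rise in visits alone (at most 100%/50% = 2.0 on these assumptions) as the inflation of cost per case, but only the visit-related share of cost scales with it.

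The primary endpoint and the between-arm effect are untouched. This is a worthwhile improvement to two secondary economic objectives, not a threat to the trial's main conclusion.

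**What to change.** Add one item per facility contact to the cost questionnaire: was this visit or trip made only on study advice or for a study blood sample, or would it have been made anyway? Report the cost-of-illness and cost-effectiveness results twice: once leaving out study-only contacts with their travel, tests and lost time, and once with all contacts included. The care advice in the case-finding section stays unchanged.

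The cost is one question per contact and one extra analysis run. The answer is partly hypothetical, which is why both results should be shown. The item would not correct for inpatient cost avoided through earlier attendance; the report should state that limitation.
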